**Figure 2 fig2:**
[figure not shown]
Flowchart of patient recruitment and study implementation.

**Table 1 tab1:** Timetable for study enrolment, intervention and evaluation.

Study period		Recruitment	Allocation	Intervention		Follow-up
Time point		0 M	0 M	0 M	3 M	6 M
Time point	Eligbility screen	√				
	Informed consent	√				
	Allocation		√			
Intervention	PMT Management			√	√	
	Control					
Assessments	Sociodemographic variables			√		
	Disease-related materials			√		
	Clinical Health Indicators			√	√	√
	Medication Self-Management			√	√	√
	Social Cognition and Psychology			√	√	√

### Study setting and randomization

2.2

The study remained single-blind, with participants unaware of their group allocation. All outcome assessors, including the triage nurses and laboratory staff, were blinded to the group assignments to minimise measurement bias. Data were collected and analysed by an independent third-party researcher and anonymised and coded to reduce measurement bias. Physiological outcome indicators were assessed at outpatient review by blinded triage nurses and laboratory staff who were unaware of subgroup information. The study population was screened from patients admitted to the inpatient Neurology Department between June and December 2025, following the inclusion and exclusion criteria, and the study will be conducted in the Neurology Department of Linyi Central Hospital, Shandong Province, China, in the first and second wards.

Eligible participants were randomly allocated to either the intervention group or the control group in a 1:1 ratio. The randomization sequence was generated by an independent biostatistician using a computer-based random number generator in SPSS (version 27.0, IBM Corp.). To ensure balance in group sizes over time, block randomization with a fixed block size of 4 was utilized. To control for potential baseline imbalances in key prognostic factors, the randomization was stratified by baseline NIHSS score (≤5 vs. > 5).

Allocation concealment was guaranteed to prevent selection bias. The randomization assignments were stored in sequentially numbered, opaque, sealed envelopes (SNOSE). These envelopes were prepared and held by an independent research coordinator who was not involved in the recruitment or assessment of participants. After a participant’s eligibility was confirmed and baseline data were collected, the recruiter would open the next envelope in sequence to determine the participant’s group assignment.

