**Methods:**

The study will conduct a single-blind, single-centre randomised controlled trial in Linyi City Central Hospital, Shandong Province, with IS patients over 18 years old. The intervention group will receive routine care combined with the AI-HEALS, while the control group will receive routine care alone. Primary outcomes include changes in medication adherence levels at baseline and 1, 3, and 6 months of follow-up. Secondary outcomes encompass medication behavior management, medication literacy, self-efficacy, social cognition, psychological levels, and clinical outcome indicators.

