### Study participants

2.3

IS patients admitted to Linyi Central Hospital in Shandong Province between June and December 2025 were selected as participants for this study. Eligibility was verified through a two-step process. First, trained staff screened electronic medical records of consecutive ischemic stroke patients. Second, a board-certified neurologist confirmed eligibility through a clinical assessment. Informed consent was obtained only after this verification was complete. Upon admission, patients will complete trial enrolment and sign a study informed consent form via face-to-face, followed by initiation of the 3-month intervention. Although participants are not recruited or initiating the intervention simultaneously, they will all follow the same intervention cycle.

To minimise the risk of cross-group contamination, we implemented stringent control measures across three dimensions: physical, personnel, and procedural. Physically, we allocated distinct follow-up times and consultation rooms for each group, with intervention materials kept under lock and key. Personnel-wise, all staff underwent standardised training, were explicitly prohibited from mentioning intervention details to the control group, and were provided with standardised response scripts. Procedurally, we implemented clear role-based segregation, advised patients at enrolment to avoid cross-group communication, and ensured effective execution of all isolation protocols through regular monitoring.

The study has been approved by the Ethics Committee of Linyi Central Hospital in Shandong Province (LCH-LW-2025031) and registration of the study protocol has been completed with the China Clinical Trial Registry (registration number: ChiCTR2500101457).

Inclusion criteria:

Meet the diagnostic criteria for first-episode ischaemic stroke (62);Age 18 years and above;Be able to operate smartphones and social media applications such as WeChat;Patients or family members signing an informed consent form.

Exclusion criteria:

Patients with cerebral haemorrhage after intravenous thrombolytic therapy;Patients with indications for mechanical thrombolysis by cerebral angiography (CTA) or other imaging tests (63, 64);Patients with severe mental illness, impaired consciousness, and inability to communicate effectively;Patients with severe gastrointestinal bleeding or serious cardiac, hepatic, or renal insufficiency;Patients with cancer or haemorrhagic disease.

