**Figure 3 fig3:**
[figure not shown]
Schematic diagram of the operation of the intervention system.

The intervention comprises a three-stage core educational programme. The first session is delivered within 48 h of admission (approximately 30 min), the second is scheduled 24–48 h prior to discharge (approximately 30 min), and the third involves remote intervention via the AI-HEALS system following discharge (continuing for approximately 3 months). The intervention is delivered using a hybrid model. The initial two in-hospital sessions comprise face-to-face, one-to-one sessions between nurses and patients, utilising mobile educational services provided by the AI-HEALS system. The post-discharge session is delivered remotely via the AI-HEALS mobile application. All neurological nurses responsible for delivering the intervention underwent mandatory standardised training led by the Head Nurse and neurological physicians. This four-hour training covered the research protocol, theoretical foundations of the intervention, and operational protocols for the AI-HEALS system. To ensure intervention fidelity, the Head Nurse conducted weekly randomised spot checks of 10% of sessions via session recordings and direct observation to verify protocol adherence. To consolidate learning outcomes, the AI-HEALS system automatically delivered daily push notifications containing key medication reminders and health alerts to the intervention group for 3 months post-discharge (see Supplementary material).

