## Outcomes

3

Primary Outcome: Change in medication adherence from baseline and at 3 and 6 months of follow-up.

Secondary outcomes:

Changes in medication self-behavior: medication literacy levels, correct medication taking, self-efficacy for rational medication use.Social cognitive and psychological: quality of life, depression, anxiety.Clinical health indicators: blood pressure (BP), low-density lipoprotein (LDL-C) level, glycated Hemoglobin (HbA1c), fasting plasma glucose (FPG), readmission rate.

The corresponding study questionnaires completed by all patients at baseline and follow-up were hosted on a web-based platform (Questionnaire Star). The questionnaires were distributed by the researchers through Questionnaire Star, and patients were instructed to complete them by the researchers either face-to-face (during hospitalisation) or by telephone (after discharge). Patient demographic information was collected through the case system and self-designed questionnaires.

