### Informed consent

6.5

All participants will voluntarily sign an informed consent form after fully understanding the purpose, methods, potential risks and benefits of the study. For patients who are unable to sign the informed consent form, the option of verbal consent will be offered and it will be ensured that they understand the study and agree to participate.

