Despite the relative rigour of our study design, some potential shortcomings require attention. Our inclusion criteria explicitly required patients to be proficient in the use of WeChat, but older adults or low-education groups may face barriers to operation. For this reason, our nurses will train patients face-to-face on the operating system at the beginning of the intervention to ensure that each subject is proficient. Our study is proposed to be implemented in Linyi City Central Hospital, Shandong Province, and sample representativeness may be limited. The generalizability of our intervention protocol may need to be verified by a multicentre trial in the future. A key limitation of this study is its single-blind design, necessitated by ethical and technical constraints. While this design risks performance bias, as staff were aware of group allocations, we mitigated this through standardized procedures. Furthermore, despite rigorous measures—including physical separation, staff training, and process management—to prevent intergroup “contamination,” we cannot entirely preclude patients encountering information about the AI-HEALS system outside the clinical setting. Such contamination would likely dilute the observed treatment effect, meaning our findings should be considered a conservative estimate. Future studies could address this by employing stricter isolation designs, such as cross-centre randomisation or the Zelen design. Due to the time constraints of the subject, although we proposed to collect data at baseline and at 3 and 6 months of follow-up, this follow-up period is still not long enough for assessing long-term efficacy, especially for a chronic disease such as stroke, and relevant studies have shown that medication adherence in stroke patients declines significantly after 1 year (43). We suggest that follow-up studies could be extended to 12 months or longer and track medication refill rates or hospitalisation rates in conjunction with health insurance data to improve the credibility of the findings. In addition, although the development and maintenance of the AI-HEALS does not require excessive funding, the updating of the Q&A knowledge base and pushed content still requires continuous follow-up by professionals. This is still a challenge for healthcare workers who are busy with their own work, and the stability of the system (e.g., server response speed) may affect the patient experience, but we have found that in the early days of the system’s creation, the stability and the corresponding speed will be gradually optimised as the AI technology advances. How to ensure that this technology can be applied within a wider range of diseases is one of the issues to be addressed in the future. As detailed in recent scoping reviews, the majority of AI applications to date have concentrated on enhancing acute diagnosis—for instance, through automated lesion segmentation and large vessel occlusion detection—and on predicting clinical outcomes (81). These tools are invaluable for rapid decision-making in the hyper-acute window. In contrast, our intervention operates in the post-acute and chronic phases of care, targeting a critical but less technologically addressed domain: secondary prevention. By providing personalized, theory-driven education, our AI system complements diagnostic and predictive models, directly empowering patients to manage their health and mitigate the risk of recurrence. This highlights a complementary and essential role for AI in extending the continuum of intelligent stroke care beyond the hospital setting.

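### Participants cannot be blind to their arm as section 2.2 states, and because the primary outcome is self-reported, the findings as a whole cannot be called conservative

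*Protocol article*

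**What the plan says.** On blinding, section 2.2 states: "The study remained single-blind, with participants unaware of their group allocation". It goes on: "All outcome assessors, including the triage nurses and laboratory staff, were blinded to the group assignments to minimise measurement bias". It adds that an independent third-party researcher collects and analyses the data, which are anonymised and coded.

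On what each arm experiences, the abstract states: "The intervention group will receive routine care combined with the AI-HEALS, while the control group will receive routine care alone". Section 2.5 describes the contact: "The initial two in-hospital sessions comprise face-to-face, one-to-one sessions between nurses and patients". A remote AI-HEALS stage follows, with daily push notifications to the intervention group for three months after discharge. Section 6.10 adds weekly telephone calls to intervention participants about technical difficulties or negative emotions. No sham app or attention control is described.

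On what participants are told, section 2.3 says that the team "advised patients at enrolment to avoid cross-group communication". Section 6.5 says that consent is signed "after fully understanding the purpose, methods, potential risks and benefits of the study".

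On the primary outcome, section 2.4 names the between-group difference in ARMS-7. Section 5.1 describes seven Likert items with a total of 7 to 28, where a higher score means poorer adherence. On how questionnaires are completed, section 3 says: "patients were instructed to complete them by the researchers either face-to-face (during hospitalisation) or by telephone (after discharge".

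On bias, section 7 says that staff knew the allocations and names performance bias on that ground. It then argues that contamination would dilute the effect, "meaning our findings should be considered a conservative estimate".

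**The concern.** A patient who has been taught one-to-one on a named system, messaged every day and telephoned every week knows which arm this is. The blinding claimed for participants is therefore a property that this design does not have.

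It matters because the patient is the source of the primary outcome. Blinding triage nurses and laboratory staff protects the physiological measures but does not stop a patient who knows the arm from rating their own adherence more favourably. On ARMS-7 that lowers the score, in the direction that favours the intervention.

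A report that carried forward both the participant-blinding statement and the conservative-estimate statement would tell readers that the primary result is protected from reporting bias and that any error runs against the intervention. The plan supports neither.

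**Working it through.** **Step 1. Can participants be unaware of their arm?**

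| Feature | Intervention | Control | Source |
|---|---|---|---|
| In-hospital teaching | Two one-to-one nurse sessions using AI-HEALS, in addition to routine care | Routine care | Abstract; 2.5 |
| After discharge | Remote AI-HEALS stage, daily pushes for 3 months | Routine care | 2.5 |
| Weekly calls | Yes | None described | 6.10 |
| Sham or attention control | Not applicable | None described | Abstract; 2.1; 2.5 |

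Nothing in the right-hand column imitates the left. Intervention patients know what they receive. Controls learn at enrolment that there is another group (2.3). At most, a control might not know what that group receives.

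**Step 2. Who administers ARMS-7?** Section 2.2 claims blinding for all outcome assessors and independent data collection. Section 3 says only that the researchers guide completion, by telephone after discharge. It does not identify them with the independent researcher, and it does not exclude nurses who deliver sessions or research assistants who make the weekly calls. This is an ambiguity, not a statement that the administrators are unblinded.

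**Step 3. Which way does the net bias run?** Write the observed benefit as D = Δ(1 − c) + b. Here Δ is the true difference, c the fraction lost to contamination, and b the extra favourable reporting in the intervention arm, in ARMS-7 points. Section 2.4 gives Δ = 1.0 (10.0 against 9.0). The documents give neither c nor b, so the values below are assumptions.

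- c = 0.20, b = 0: D = 0.80, diluted, as section 7 says.
- c = 0.20, b = 0.25: D = 0.80 + 0.25 = 1.05, above the truth.
- c = 0.30, b = 0.25: D = 0.70 + 0.25 = 0.95, below the truth.

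The sign of the net bias depends on whether b exceeds cΔ, and nothing in the documents settles that.

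**Step 4. How much could a reporting shift matter?** No figure in the plan is being reproduced here; this is an illustration. From section 2.4: SD 2.0, two-sided α 0.05, 40 per group recruited, 32 per group after the 20% attrition allowance. With no true effect and a reporting shift of b points:

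- SE = SD × √(2/n). For n = 40, 2.0 × √(2/40) = 0.447. For n = 32, 2.0 × √(2/32) = 0.500.
- Rejection rate = Φ(b/SE − 1.96) + Φ(−b/SE − 1.96).

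| Assumed b (points) | 40 per group | 32 per group |
|---|---|---|
| 0 | 5.0% | 5.0% |
| 0.25 | 8.6% | 7.9% |
| 0.5 | 20.1% | 17.0% |
| 1.0 | 60.9% | 51.6% |

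For scale, one item moved by one category is 1 point. A mean shift of 0.25 therefore needs a quarter of intervention patients to move one item by one category more than controls do; a mean shift of 0.5 needs half of them.

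**The case against.** Nothing in the document rescues the participant-blinding sentence, but several objections limit what can be built on it.

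*Assessor blinding.* A reader might infer that only triage and laboratory staff are blinded and that ARMS-7 is taken by unblinded staff. The text does not support that. Section 2.2 covers all outcome assessors, naming those two groups as included, and provides for independent collection. The remark in section 7 that staff knew the allocations explains performance bias and reads most naturally as those delivering care. What stands is that section 3 does not connect its researchers to the blinded, independent person.

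*The contamination argument.* A reader might infer that the conservative-estimate sentence is simply false, or that the trial must overstate its effect. Neither follows. Contamination taken alone does dilute, and performance bias is named nearby. What fails is the step from contamination to the findings as a whole, with participant reporting bias left out.

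*Size.* A reader might infer that reporting bias could readily produce the whole planned 1.0 point. That would need an average shift of one category on one item across the entire intervention arm, with no matching over-reporting by controls. The assumed control mean is 10.0 and the floor is 7, so many patients have little room to move. The larger shifts are therefore less plausible.

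*Timing.* Section 2.4 sizes the trial on the end of the study period, and the last visit is at 6 months. Daily pushes stop three months after discharge, so the argument is stronger for the 3-month score.

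*Consent.* Section 6.5 is general and the consent form is not shown. It does not prove what controls know about the other arm, and the point does not depend on it.

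**Conclusion.** The point holds in this form. The statement that participants are unaware of their allocation is incompatible with the intervention and control conditions described in the same document. Because ARMS-7 is self-reported, this exposes the primary outcome to reporting bias, plausibly towards the intervention. Whether those who administer it are blinded is asserted in general terms in section 2.2 but not secured in section 3. The conservative conclusion in section 7 is valid for contamination only; for the findings as a whole the net direction of bias is unknown.

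The documents do not give the size of the bias. Under the plan's SD of 2.0, a normal approximation, 40 per group and no true effect, an assumed shift of 0.25 to 0.5 point would raise the false-positive rate from 5% to about 9% to 20%. This shows sensitivity to a modest shift and is not evidence that such a shift will occur. An open-label behavioural trial is acceptable; the fault lies in how this one is described and in what is concluded from that description.

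**What to change.** - **Section 2.2:** state that participants and the staff who deliver the intervention are not blinded. State that outcome assessors and the data analyst are, provided that this is the arrangement in practice.
- **Section 3:** state that the independent third-party researcher named in section 2.2, blind to arm, administers the 3- and 6-month questionnaires, using a script that asks patients not to reveal their group. State that staff who deliver sessions or make the weekly calls do not take part.
- **Section 7:** list reporting bias by unblinded participants as a limitation. Keep the dilution statement for contamination only and withdraw the overall conservative-estimate conclusion, saying that the two biases can oppose each other and that the net direction is not known.

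Blinded administration reduces the interviewer's influence. It does not remove self-report bias, so the limitation is needed even if the section 3 change is made.

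The cost is wording in three sections, a small reassignment of existing staff, and the loss of a blinding claim that the design cannot support. Sample size, intervention and endpoint are unaffected by this point.

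### Fixed blocks of four, with envelopes opened by the recruiter, leave about one third of assignments deducible to anyone who knows the block size, so concealment is not guaranteed

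*Protocol article*

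**What the plan says.** Section 2.2 of the protocol article (Study setting and randomization) says that participants are "randomly allocated to either the intervention group or the control group in a 1:1 ratio" and that "block randomization with a fixed block size of 4 was utilized". There is one binary stratification factor, the baseline NIHSS score, cut at 5.

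Assignments are kept in opaque, sealed envelopes in numbered order, prepared and held by an independent coordinator. The opening step follows confirmation of eligibility and the baseline assessment; at that stage, according to the text, "the recruiter would open the next envelope in sequence to determine the participant’s group assignment". The same section says: "Allocation concealment was guaranteed to prevent selection bias".

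Section 7 (Discussion) accepts a risk of performance bias "as staff were aware of group allocations". It does not mention predictability of the sequence.

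Section 2.3 (Study participants) describes two-step verification of eligibility. Staff go through the records of consecutive patients, then a neurologist confirms eligibility clinically, and consent follows. Entry depends partly on whether the patient can use WeChat and can communicate.

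**The concern.** Opaque envelopes hide what is printed inside them. They do not hide what follows from the envelopes already opened. In a block of four with two places per arm, the fourth assignment is always fixed by the first three, and the third is fixed whenever the first two agree. With one centre, two strata and a single block size, the sequence is easy to follow, and the stated procedure shows the recruiting side each allocation as it is made.

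What is at stake is selection bias at entry. If someone involved in approach, consent or a judgement-based criterion can tell which arm comes next, more motivated or app-capable patients could be favoured for the intervention. The primary outcome is a self-reported adherence scale, and the planned difference is 1.0 ARMS-7 point with 40 per group, so modest steering could matter. Adjustment for baseline measures could reduce bias acting through what is measured, but not through unmeasured motivation.

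**Working it through.** The article gives no predictability figure, so there is none to reproduce.

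**Inputs.** Section 2.2 gives block size 4, 1:1 allocation (2 + 2 per block) and two strata. Section 2.4 gives 80 patients. It is assumed that each stratum has its own envelope sequence, as stratified blocks require; the text mentions only one next envelope and does not say this outright. The observer is assumed to know the block size, the stratum and the earlier allocations in that stratum.

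**Assignments forced with certainty.** There are C(4,2) = 6 equally likely blocks.
- AABB and BBAA force the last two assignments: 2 × 2 = 4.
- The other four blocks force only the last one: 4 × 1 = 4.
- Expected forced per block = (4 + 4)/6 = 1.333. Share = 1.333/4 = 33.3%.
- By position in the block, the probability of being forced is 0, 0, 1/3 and 1.

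**Number out of 80.** This depends on how the strata split, because the last block in a stratum may be incomplete.
- Both strata multiples of 4: 20 blocks × 4/3 = 26.7 (33.3%).
- Remainders 1 and 3: 19 × 4/3 + 1/3 = 25.7 (32.1%).
- Remainders 2 and 2: 19 × 4/3 = 25.3 (31.7%).

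The expected number is therefore 25.3 to 26.7.

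**Best guess (always name the arm that is behind in the block).** The probability of being right is 1/2 at position 1 and 2/3 at position 2. At position 3 it is 1/3 × 1 + 2/3 × 1/2 = 2/3, and at position 4 it is 1. The mean is (1/2 + 2/3 + 2/3 + 1)/4 = 17/24 = 70.8%, against 50% if nothing could be inferred.

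**Effect of varying the block size.** This was simulated (4,000 runs of 40 patients in one stratum) for an observer who knows the possible sizes but not their order.

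| Block sizes | Forced with certainty | Best guess right |
|---|---|---|
| 4, fixed | 33.3% | 70.8% |
| 4 and 6 | 5.6% | 68.9% |
| 2, 4 and 6 | 4.0% | 70.0% |
| 4, 6 and 8 | 2.3% | 67.6% |

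Varying the size removes most of the certainty but little of the guessing advantage.

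**Cost in balance.** The largest imbalance within a stratum is half the block size: 2 with blocks of 4, and 3 with blocks of up to 6. Over two strata the worst case is 3 + 3 = 6, for example 43 against 37. The variance factor for the group difference is then 1/43 + 1/37 = 0.0503, against 2/40 = 0.0500 with equal groups.

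**The case against.** The strongest reply is that the arithmetic describes what could be deduced, not what anyone knew. Deduction needs one person to hold the block size, the stratum and the full run of earlier allocations in it. The article does not say that recruiters were told the block size, or that one person opened every envelope; the trial runs in two wards. Printing the block size in the article does not show that recruiters had it while envelopes were being opened. All of this stands, and it is why the point is worded as deducible rather than known.

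A reader might also infer that recruiters choose whom to approach and themselves judge smartphone ability. The documents do not say so. Section 2.3 describes consecutive screening and confirmation by a neurologist, which narrows the room for steering. It does not close it. Consent is still sought patient by patient, two of the criteria call for judgement, and nothing says that those who screen or confirm eligibility are unaware of earlier allocations.

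The Discussion's remark about staff awareness concerns performance bias and does not show that anyone tracked the sequence. It does show that past allocations were not hidden from staff.

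On the remedy, opening after baseline is already specified, and the arm must still be announced to those who deliver care. Moving the opening to the coordinator therefore does not stop tracking. What it adds is an independent check that entry is irrevocable before the arm is revealed. Fixed small blocks are also a common design, and there is no internal contradiction or numerical error here.

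**Conclusion.** The point holds as a design weakness and an overstated claim. To someone who knows the block size and the earlier allocations in a stratum, about one third of assignments (25.3 to 26.7 of 80) are deducible before enrolment, and the next arm can be guessed correctly 70.8% of the time. The envelope procedure does not prevent this, so the word guaranteed is not supported.

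The figures assume separate sequences per stratum and an observer who has followed them. The documents do not establish that recruiters knew the block size, that they predicted allocations, or that any patient was steered. A reader should not conclude that selection bias occurred, or that no analysis could reduce it. This is an improvement that should be made because it is cheap; it does not by itself invalidate the trial.

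**What to change.** For envelopes not yet used:
- The independent biostatistician regenerates the list within each NIHSS stratum with randomly varying block sizes (for example 4 and 6), and neither the sizes nor their order are disclosed to site staff. Starting the new list once the open block in each stratum is finished keeps the imbalance within the limit shown above.
- The independent coordinator, who already holds the envelopes, opens the next one only after the patient is irrevocably entered and baseline is complete.

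Both parts are needed, because varying the block size alone leaves best-guess accuracy at about 69%. The cost is a new list and a change in who opens the envelope, using people already named, plus a possible imbalance of up to 3 patients per stratum instead of 2.

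In Section 2.2, replace the statement that concealment was guaranteed with a description of the procedure, including whether each stratum has its own envelopes. If recruitment is complete, state who knew the block size and who opened the envelopes, and add predictability of the sequence to the limitations in the Discussion. That costs only a text change.
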